##### Demographics

At T0, we will collect sex, age, race and ethnicity, level of education, insurance, marital status, smokeless tobacco use, cannabis use, chronic health conditions, and prior use of guided mental imagery.

##### Tobacco Use

At T0, T1, and T2, we will collect tobacco use status using a series of questions that have been standardized and used in previous studies [25-27] and the level of dependence using the Fagerström Tolerance Nicotine Dependence Scale [28].

##### Self-Efficacy for Quitting

We will measure self-efficacy for quitting smoking with an abbreviated version of the Condiotte and Lichtenstein Confidence Questionnaire [29].

##### Cravings

All participants will be asked to rate their experience with withdrawal symptoms and cravings using the Nicotine Dependence Syndrome Scale [30] at each follow-up assessment.

##### Expectancies and Credibility

We will include items adapted from the Borkovec and Nau Treatment Credibility Scale [31] and used in our completed GI mobile app study to measure expectancies and perceived credibility of GI for smoking cessation [11,23]. We will also adapt this measure to assess for expectancies and perceived credibility of the behavioral program used in the BC.

##### Consumer Satisfaction Measure

At T1, participants will complete a consumer satisfaction survey that we have used in our previous research [25,32] and consists of up to 11 items (using a 5-point Likert scale), measuring overall satisfaction with the program in each study condition, perceived usefulness and relevance of the information, likeability, the level of interest, and the ease of use, as well as whether they would recommend the program to others.

##### Intervention Adherence

Adherence will be measured by a composite of self-reported minutes of intervention use per week, the number of times skills practiced per week, the number of sessions attended, and coach-rated participant engagement in sessions.

##### Imagery Vividness and Sociotechnical and Ethical Outcomes

At T0, T1, and T2, we will assess participants’ perceptions about the effectiveness of GI for tobacco cessation and their vividness of visual imagery using the Vividness of Visual Imagery Questionnaire, which we have adapted to include images of smoking [33]. At T1, we will examine participants’ use of GI during the RCT and their perception of the GI program’s *fit* in their lives through semistructured in-depth interviews [34,35].

##### Biochemical Verification of Tobacco Abstinence

All participants who self-report 7-day abstinence at the 6-month assessment will be selected for biochemical verification. We will (1) use enhanced collection procedures, including contact with participants via telephone before the assessment and via video call during the assessment if participants request assistance; (2) provide an iCO Smokerlyzer expired CO monitor (Bedfont Scientific Limited) to each participant who reports abstinence, a procedure that has been used successfully in previous remote collection studies and has high accuracy [36-38]; and (3) provide an incentive of US $50 for the completion of the biochemical assessment.

##### Biomarkers

Expired CO will be measured among smokers using iCO Smokerlyzer personal CO monitors. A monitor will be sent to each participant who reports abstinence at the 6-month follow-up assessment. Each participant will exhale into the monitor according to instructions. Readings are measured in parts per million. A cutoff of <6 parts per million is recommended [39]. The results will be transmitted electronically to the research team.

##### Collection Procedures

Project staff will contact participants who report abstinence at the 6-month assessment via SMS text message, telephone, or email to schedule a HIPAA-compliant encrypted video call during which biochemical verification will be completed. On the scheduled day of assessment, project staff will verify the participant’s identity through the confirmation of their name and face from a photograph ID. During this session, project staff will provide step-by-step instructions for completing biochemical verification.

#### Outcomes

Our primary outcome is self-reported 30-day abstinence as measured at the 6-month assessment. Secondary outcomes include self-reported 7-day abstinence as well as biochemically verified 7-day abstinence at the 6-month assessment and, for nonquitters, cigarettes smoked per day.

We will also examine the effect of adherence to the GI on cessation outcomes, conduct subgroup analyses of moderators (eg, recruitment method, location, sex, race and ethnicity, and level of dependence) on tobacco cessation outcomes at 6 months, and use a mixed methods approach (eg, surveys and in-depth interviews) to explore subgroup differences in GI adherence and cessation outcomes.

#### Qualitative Subgroup Study

Subsample participants (36/1200, 3%) will be recruited after a preliminary analysis of the T1 data and based on the following criteria: recruitment method, location, sex, race and ethnicity, and abstinence status. After a quantitative analysis of the subgroups, the team will identify 36 participants through purposive sampling (eg, identifying participants who were recruited through community methods). Only those participants who indicate an interest in participating in in-depth interviews at T1 will be invited to participate in in-depth interviews via telephone, email, or SMS text message. One-hour telephone interviews will be conducted by a member of the study team, who will use a semistructured interview guide to explore the following aspects: program use during the RCT (eg, how did the technology they used influence completion of coaching calls?), their perceptions of program effectiveness for tobacco cessation (eg, how does GI work to help them stop smoking?), and their perception of the program’s *fit* in their lives (eg, how does GI integrate or not integrate with their lifestyle?).

#### Power and Sample Size

A sample size of 1200 participants would yield 90% power to detect a difference in smoking cessation rates between the arms of 10%, assuming a control arm cessation rate of 0.30, a 20% dropout, and a noncontinuity-corrected chi-square test at a 2-tailed significance level of 5%. We believe that 10% is a clinically significant difference with positive public health implications. Although the control arm had a higher cessation rate in our pilot study (50%) [19], we believe that this rate was unusually high. Furthermore, the rates were self-report, not biochemically verified, which are estimated to be 10% to 50% lower [39]. It was also high compared with quitline cessation rates, which are closer to 30% to 40% [15,40].

This sample size also yields 90% power to detect small-to-medium standardized effect sizes for continuous secondary outcomes of Cohen *d*=0.28, using a Bonferroni correction to account for multiplicity (20 tests), assuming a 2-sided 2-sample *t* test. Aim 3 will investigate effect modification, which requires approximately 4 times the sample size (or, equivalently, results in a larger detectable effect size) [41]. Assuming that a subgroup of interest makes up 50% of the sample, we have 90% power to detect a difference in cessation rates of 0.141 and 80% to 90% power to detect standardized effect sizes of 0.26 to 0.30, assuming no multiple testing correction. We recognize that the inputs to these calculations are estimates only.

Table 2 displays a sensitivity analysis, showing power for control arm cessation rates of 0.20 and 0.40, dropout rates of 20% to 40% (typical range for cessation trials), and differences of 0.10 to 0.15, showing ample power for different scenarios. These power calculations are conservative; simulation studies demonstrate that mixed effects models (the proposed analyses [Data Analysis subsection]) yield more power than chi-square and *t* tests [42,43].

**Table 2 table2:** Sensitivity analysis (N=1200).

Dropouts, n^a^	Cessation rate: 0.20			Cessation rate: 0.40	
	Detectable difference: 0.10	Detectable difference: 0.15	Detectable difference: 0.10		Detectable difference: 0.15
240	0.95	0.99	0.88		0.99
360	0.92	0.99	0.83		0.99
480	0.87	0.99	0.77		0.98

^a^Dropout rate: 20% (n=240); 30% (n=360); 40% (n=480).

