### Phase 2: RCT

#### Study Design

This 2-group RCT will test the efficacy of the integrative GIC versus the evidence-based BC. Participants will be recruited from 3 states (Arizona, New York State, and West Virginia). We will randomize 1200 participants to either the GIC or the BC. Of these 1200 participants, 600 (50%) will be recruited through the quitlines (n=200, 33.3%, per quitline) and 600 (50%) through population-based methods (eg, social media, earned media, local organizations, and health care providers) to ensure that we obtain a representative sample of smokers (Figure 1). Assessments will occur at T0, T1, and T2. The research team will deliver the intervention and control protocols, coordinate and conduct all assessments, and perform all data analyses at the University of Arizona.

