##### Randomization

Participants are stratified by state and method of recruitment (ie, quitline or community) and then randomized automatically in REDCap using a randomization table created by the study biostatistician. Statistical software was used to create a randomized-block allocation to the GIC or the BC, stratified by recruitment method and location.

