#### Data Analysis

##### Overview

This is a 2-arm parallel RCT where the primary outcome is self-reported 30-day abstinence at 6 months. Questionnaires will be scored according to developer instructions. In the case of missing items, where developers do not have explicit instructions, we will use a half-mean imputation rule, as outlined in Bell et al [44]. All analyses will be adjusted for the randomization stratification. The primary analysis will use a significance level of .05; other tests will use a Bonferroni correction for multiple comparisons to control the overall type I error at 5%. Demographics, including sex, will be described with means, SDs, ranges, and frequencies or proportions and explored as correlates for successful tobacco outcomes using appropriate regression models.

##### Aim 1

We will test the efficacy of a telephone-delivered GI tobacco cessation treatment versus an evidence-based behavioral treatment on self-reported 30-day abstinence from smoking at T2. Secondary outcomes include self-reported and biochemically verified 7-day point prevalence abstinence at T2.

##### Hypothesis 1

Participants in the GIC will have 10% higher quit rates than those in the BC.

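### The 90% power at d = 0.28 is stated for all continuous secondary outcomes, but it does not cover the between-arm comparison of cigarettes per day in nonquitters, where it is about 67%

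*Protocol article*

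**What the plan says.** All references are to the protocol article.

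- **Power and Sample Size** sizes the trial on the primary outcome, "assuming a control arm cessation rate of 0.30, a 20% dropout, and a noncontinuity-corrected chi-square test at a 2-tailed significance level of 5" percent. It then claims "90% power to detect small-to-medium standardized effect sizes for continuous secondary outcomes of Cohen" *d* = "0.28, using a Bonferroni correction to account for multiplicity (20 tests), assuming a 2-sided 2-sample" *t* test. No continuous secondary outcome is excepted.
- **Outcomes** lists three secondary outcomes. Two are binary (7-day abstinence, self-reported and biochemically verified). The third is introduced by "and, for nonquitters, cigarettes smoked per day".
- **Data Analysis, Aim 2 (text under Hypothesis 2B)** plans regression models that compare tobacco use at 6 months between guided imagery participants who have not quit and the control group. It also plans to look at change from baseline.
- **Data Analysis, Aim 1 (text under Hypothesis 1)** also names nicotine dependence, self-efficacy and cravings as secondary outcomes. Table 1 schedules them at all three assessments, with no restriction to nonquitters.
- **Data Analysis, Overview** says that "other tests will use a Bonferroni correction for multiple comparisons to control the overall type I error at 5" percent.

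**The concern.** An outcome defined only in people still smoking loses everyone who quits, and the plan expects 30% to 40% of retained participants to quit. The power section uses those quit rates for the primary outcome. It does not carry them over to the secondary outcome whose sample they reduce. If the 90% figure needs every retained participant, a reader would credit the cigarettes-per-day comparison with power that the design does not give it. A null between-arm result among nonquitters could then be taken as good evidence against an effect of d = 0.28, when the chance of missing such an effect is about one in three rather than one in ten.

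**Working it through.** **Inputs**

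- Total randomized: 1200 (Study Design).
- Allocation: 1:1, 600 per arm. This is an assumption, as the ratio is not stated. It reproduces the primary power and Table 2.
- Dropout 20%: 600 × 0.80 = 480 per arm, 960 in all (Power and Sample Size).
- Quit rates: 0.30 in control and 0.30 + 0.10 = 0.40 in guided imagery (Power and Sample Size).
- Alpha: 0.05 / 20 = 0.0025, two-sided, with a two-sample *t* test (Power and Sample Size).

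**Formula.** The noncentrality is λ = d × √(n₁n₂ / (n₁ + n₂)). Power is close to Φ(λ − z), with z = 3.023 for two-sided alpha 0.0025. The results below use the noncentral *t* distribution, with the normal approximation as a check.

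**Step 1: reproduce the plan's figures.**

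- Primary outcome, 480 per arm, 0.30 v 0.40: power 0.902 (stated 90%).
- Continuous outcome, 480 per arm: √(480 × 480 / 960) = 15.49, so λ = 0.28 × 15.49 = 4.34. Power is 0.904 (normal 0.906), and d for 90% power is 0.279. This matches the plan.
- With 600 per arm (no dropout), power would be 0.965 and d for 90% power 0.249. The stated figure therefore rests on 480 per arm, that is, on every retained participant contributing a value.

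**Step 2: the same calculation in nonquitters.**

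- Control: 480 × (1 − 0.30) = 336. Guided imagery: 480 × (1 − 0.40) = 288.
- √(336 × 288 / 624) = 12.45, so λ = 0.28 × 12.45 = 3.49.
- Power is 0.674 (normal 0.679), and d for 90% power is 0.347.

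**Step 3: range over the plan's own uncertainty.** Quit-rate difference 0.10; each cell gives nonquitters (control v guided imagery), power at d = 0.28, and d for 90% power.

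| Quit rates | 20% dropout | 30% dropout | 40% dropout |
|---|---|---|---|
| 0.20 v 0.30 | 384 v 336: 0.762; 0.323 | 336 v 294: 0.681; 0.345 | 288 v 252: 0.583; 0.373 |
| 0.30 v 0.40 | 336 v 288: 0.674; 0.347 | 294 v 252: 0.589; 0.371 | 252 v 216: 0.493; 0.401 |
| 0.40 v 0.50 | 288 v 240: 0.566; 0.378 | 252 v 210: 0.483; 0.404 | 216 v 180: 0.396; 0.437 |

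No cell reaches 90%. Higher dropout alone accounts for part of the fall: with every retained participant contributing, power is 0.847 at 30% dropout and 0.765 at 40%. The 20% column isolates the effect of restricting to nonquitters.

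**Step 4: two further checks.** If guided imagery has no effect on quitting (0.30 in both arms, 336 v 336, 20% dropout), power is 0.724. Without the 20-test correction (alpha 0.05), power for 336 v 288 is 0.936. The shortfall thus comes from the smaller sample combined with the strict alpha.

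**The case against.** The strongest reply is that nothing was miscalculated. The list under Outcomes is introduced as inclusive, not complete, and Data Analysis names three continuous scales measured in everyone. Those are natural referents of the power sentence, and 90% is right for them. This stands. A reader might infer that the stated power is an arithmetic error, or that it fails for the continuous secondary outcomes in general. The documents support neither. What remains is that the sentence speaks for the whole class, and a declared member of that class does not fit.

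A second reply is that the formal hypothesis about nonquitters, Hypothesis 2B, concerns a reduction from baseline within participants, to which a two-sample power does not apply. This also stands, and it would be wrong to infer that Hypothesis 2B has only 67% power. As an illustration, if the change within an arm were 0.28 SD of the change score (an assumption), power at alpha 0.0025 would be about 0.95 with 288 participants and 0.98 with 336. But Aim 2 plans a between-arm comparison as well, and the 67% belongs to that.

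Third, baseline adjustment could recover power. Tobacco use is collected at baseline, so this is possible. The plan does not state such adjustment for this model and gives no correlation, so the gain cannot be computed from the documents. Under assumed baseline correlations of 0.3, 0.5 and 0.6, power for 336 v 288 would be about 0.73, 0.84 and 0.91. The power section's own claim to be conservative does not settle this: it rests on mixed models, whereas regression models are named for the nonquitter comparison.

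Finally, the section warns that its inputs are only estimates. That covers uncertain rates and dropout. It does not cover using the full retained sample for an outcome defined in part of it.

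**Conclusion.** The point holds as a minor error of scope. The 90% at d = 0.28 is correct for continuous scales measured in all 960 retained participants. It is not correct for the between-arm comparison of cigarettes per day in nonquitters, where power is about 67% and d of about 0.35 is needed for 90%.

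These figures assume 1:1 allocation, nonquitters defined by the 30-day outcome among those retained, the planned 0.30 and 0.40 quit rates with 20% dropout, an unadjusted *t* test, and the 20-test Bonferroni threshold applied to this outcome. The primary power is unaffected, so it would be wrong to infer that the trial is too small for its main question.

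**What to change.** In Power and Sample Size, limit the d = 0.28 statement to continuous scales measured in all retained participants, and name them (nicotine dependence, self-efficacy, cravings). Add one sentence for the between-arm comparison of cigarettes per day in nonquitters: about 336 and 288 participants under the planning assumptions, a detectable d of about 0.35 with 90% power, and about 67% power at d = 0.28. Note there that baseline adjustment could raise this power by an amount that cannot be computed from the figures given, and that the figure does not apply to the within-person reduction in Hypothesis 2B.

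The cost is one restated sentence and one added. Sample size, analysis and design stay as they are.

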##### Hypothesis 2B

Participants not reporting abstinence will report statistically significant reductions in tobacco use.

We will investigate a dose-response effect of intervention engagement using logistic regression for cessation at 6 months and linear regression for dependence, self-efficacy, and so on, with adherence. Mediation models using a causal framework will also be used [17]. We will compare self-reported tobacco use levels in GI participants who have not quit at 6 months with the control group using regression models and also investigate their changes from T0 use. Consumer satisfaction will be described with summary statistics.

##### Aim 3

We will conduct subgroup analyses of moderators (eg, recruitment method, location, sex, race and ethnicity, and the level of dependence) on tobacco cessation outcomes at 6 months and assess participants using a mixed methods approach (eg, surveys and in-depth interviews) for exploring subgroup differences.

Logistic regression models will be used to investigate effect modification of the intervention effect on abstinence at 6 months by various moderators. These regression models will include interaction terms, and if statistically significant, a stratified (by moderator) analysis will be performed and reported.

Qualitative interviews will be recorded, transcribed, and consensus coded for themes by 2 coders to guarantee intercoder reliability [48,49]. The team will document variation in the subgroups’ reported program use during the RCT, including perceptions of the program’s effectiveness and ease of use.

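### The Aim 3 power figures (0.141; d=0.26 to 0.30) are treatment effects detectable inside one half-sample subgroup, not detectable interactions, which are what Aim 3 will test

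*Protocol article*

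**What the plan says.** Power and Sample Size (protocol article) first gives the primary calculation: "A sample size of 1200 participants would yield 90% power to detect a difference in smoking cessation rates between the arms of 10" percentage points, "assuming a control arm cessation rate of 0.30, a 20% dropout" and "a noncontinuity-corrected chi-square test at a 2-tailed significance level of 5" percent. Turning to moderators, it says "Aim 3 will investigate effect modification, which requires approximately 4 times the sample size", or equivalently a larger detectable effect. The next sentence takes a subgroup of half the participants and states "we have 90% power to detect a difference in cessation rates of 0.141". It adds 80% to 90% power for standardized effects of 0.26 to 0.30, and notes that no multiplicity correction is applied.

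Data Analysis, Aim 3, names the test as logistic regression for abstinence at 6 months: "These regression models will include interaction terms, and if statistically significant, a stratified (by moderator) analysis will be performed and reported". Data Analysis, Overview, reserves the 5% level for the primary analysis and says that "other tests will use a Bonferroni correction for multiple comparisons to control the overall type I error at 5" percent.

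**The concern.** The Aim 3 figures come directly after a sentence about effect modification, so a reader will take them as the power of the Aim 3 test. That sentence and the figures do not agree. At a fixed sample size, needing four times the participants means that the detectable effect doubles, from about 0.10 for the main effect to about 0.20. The stated 0.141 is larger than the main effect only by a factor of √2, which is the cost of halving the sample.

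The within-subgroup comparison that the figures do describe is reached only after a significant interaction. The document gives no power for that first step. At stake is how informative a reader believes the moderator results can be, for recruitment route, state, sex, race and ethnicity, and dependence.

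**Working it through.** **Inputs.** From Power and Sample Size: N=1200, 20% dropout (960 analysed), control rate 0.30, two-sided 5%, subgroup share 50%. Assumed: 1:1 allocation. Randomization gives no ratio ("Statistical software was used to create a randomized-block allocation to the GIC or the BC, stratified by recruitment method and location"), but 1:1 reproduces the other power figures. This gives 480 per arm overall and 240 in each arm-by-subgroup cell.

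**1. The protocol's other figures.** The uncorrected chi-square with 480 per arm, 0.30 v 0.40, gives power 0.902. The Bonferroni figure for continuous outcomes (d=0.28, alpha 0.05/20) gives 0.906. The Table 2 cells also reproduce.

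**2. The Aim 3 figures, as one comparison inside a half-sample subgroup (240 v 240).**
- Binary, unpooled: SE = √[(0.30×0.70 + 0.441×0.559)/240] = √(0.4565/240) = 0.0436. Power = Φ(0.141/0.0436 − 1.96) = 0.898. The pooled chi-square gives 0.895. The difference detectable with 90% power is 0.1414 unpooled (0.1423 pooled).
- Continuous: SE = √(2/240) = 0.0913. Power is Φ(0.26/0.0913 − 1.96) = 0.813 and Φ(0.30/0.0913 − 1.96) = 0.908.
- Without dropout (300 per arm), power at 0.141 would be 0.949, which does not fit.

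So the stated figures are within-subgroup effects.

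**3. The protocol's own four-times rule.** The main effect detectable with 90% power is 0.0996. Halving the sample gives √2 × 0.0996 = 0.141. A four-fold requirement gives √4 × 0.0996 = 0.199.

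**4. The interaction test.** Four cells of 240, with rates 0.30, 0.30, 0.30 and 0.441: no effect in one half, 0.141 in the other.
- Risk-difference scale: SE = √[(3×0.21 + 0.2465)/240] = 0.0604. Power = Φ(0.141/0.0604 − 1.96) = 0.645.
- Logit scale, as planned: logit(0.441) − logit(0.30) = 0.610. SE = √[(3/0.21 + 1/0.2465)/240] = 0.2765. Power = Φ(0.610/0.2765 − 1.96) = 0.598.
- Continuous: SE = √(4/240) = 0.1291. Power is Φ(0.26/0.1291 − 1.96) = 0.52 and Φ(0.30/0.1291 − 1.96) = 0.64.

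Other patterns with the same 0.141 interaction and control rate 0.30 give 63% to 67% on the risk-difference scale and 56% to 67% on the logit scale.

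**5. Detectable interactions (two-sided 5%).**

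| Scale | 80% power | 90% power |
|---|---|---|
| Risk difference | 0.170 | 0.196 |
| Logistic model, as the difference in rates | 0.18 | 0.21 |
| Continuous, d | 0.36 | 0.42 |

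**6. Multiplicity, as an illustration only.** The document does not fix the number of Aim 3 tests. The five moderators are listed as examples, and the 20 tests in the power text belong to continuous secondary outcomes. With 5 tests (alpha 0.01), power at 0.141 is 36% on the logit scale and 40% on the risk-difference scale. With 20 tests (alpha 0.0025) it is 21% and 25%.

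**The case against.** Read literally, the sentence is correct. It posits a subgroup of half the sample and gives a difference in cessation rates. It never calls 0.141 an interaction, and the arithmetic is right for a within-subgroup comparison. Aim 3 is described as subgroup analyses, includes a stratified step, and carries no hypothesis, unlike Aims 1 and 2. The section itself warns that effect modification needs a much larger sample, calls its inputs estimates, and discloses that no correction is applied.

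Much of this stands, and it limits the point. A reader might infer that the 90% was miscalculated and is really 64%. The documents do not support that: the sum is right for another quantity, and 64% or 60% applies only if 0.141 is taken as an interaction. The 64% is also not one firm value, since it depends on the scale and the effect pattern, and d=0.26 was stated at the 80% end, where the interaction power is 52%. A reader might also infer that the plan's Bonferroni rule brings power to 25% to 40%. That rests on assumed families of 20 and 5 tests. Nor does the document say that a non-significant interaction will be read as a uniform effect.

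What does not fall away is the placement. The figures are offered as the quantification of effect modification. They contradict the rule in the sentence before them and do not describe the test in the analysis section. Uncertain inputs do not explain the use of a different contrast.

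**Conclusion.** The point holds as a mismatch between the stated power and the planned test. The figures 0.141 and d=0.26 to 0.30 are detectable treatment effects within one half-sample subgroup, and the article gives no power for the interaction test that comes first. For effects of the stated size, that test has about 60% power (logit) or 64.5% (risk difference) at 0.141, 52% at d=0.26 and 64% at d=0.30.

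This rests on 1:1 allocation, 960 analysed, a control rate of 0.30 in both halves, no effect in one half, a two-level moderator split 50/50, and no multiplicity correction. Unequal splits or moderators with more levels would usually lower power further.

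The lack of correction is a disclosed inconsistency with the Overview of the Data Analysis, not a concealed error. Severity: should-fix. The primary power figure is unaffected.

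**What to change.** 1. Label 0.141 and d=0.26 to 0.30 as treatment effects detectable within a subgroup of half the sample.
2. State the interaction figures separately, on the scale of the planned model. Under the logistic model, the difference in treatment effects is about 0.21 for 90% power and 0.18 for 80%. On the risk-difference scale it is about 0.20 and 0.17. For continuous outcomes, d is about 0.42 and 0.36. Name the scale: the rounded risk-difference value of 0.20 has only about 87% power under the logistic model.
3. Make the significance level in the Aim 3 power text agree with the Bonferroni rule in the analysis text, which requires fixing the number of Aim 3 tests.
4. Report each interaction with its confidence interval.

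The cost is a less favourable stated figure for a secondary aim. Enrolment and the primary analysis stay as they are.
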